## 1. INTRODUCTION

### 1.1 SUMMARY

The combination of heavy alcohol consumption and HIV infection is associated with increased mortality, HIV disease progression, acute myocardial infarction (AMI) and a proinflammatory state characterized by increased biomarker levels of inflammation. Heavy alcohol use and HIV infection are both causes of microbial translocation, the process by which bacterial products from the gastrointestinal (GI) tract leak across the GI membrane to the portal circulation. Microbial translocation causes immune activation leading to end organ damage. Alcohol can cause microbial translocation via zinc deficiency. Zinc deficiency is common among HIV+ heavy drinkers and linked to high mortality rates. Zinc supplementation is affordable, available, does not interfere with ART, and has minimal adverse drug reactions. In animal models zinc reduces ethanol associated microbial translocation. In human studies zinc slows HIV disease progression and reduces levels of inflammatory biomarkers which are strongly linked to mortality. Given zinc's potential efficacy we will conduct Zinc for INflammation and Chronic disease in HIV (ZINC HIV), a double-blinded randomized controlled trial to assess the efficacy of zinc supplementation vs. placebo among 250 HIV+ Russians, who are ART-naïve at enrollment and have a recent history of heavy drinking. Our specific aims will test the efficacy of zinc supplementation, compared to placebo to (1) improve markers of mortality as measured by the VACS index; (2) slow HIV disease progression as measured by CD4 cell count; (3) improve markers of AMI risk as measured by the Reynolds risk score; and (4) lower levels of microbial translocation and inflammation as measured by serum biomarkers. We hypothesize that as compared with placebo, patients receiving zinc supplementation will have significantly lower AMI and mortality risk as measured by the VACS index and Reynolds risk scores; higher CD4 cell counts; lower levels of biomarkers for microbial translocation and inflammation. Importantly, if our hypotheses are true, zinc supplementation could ultimately become a standard adjunctive therapy complementing alcohol interventions among HIV+ persons even in resource limited environments.

### 1.2 SIGNIFICANCE

The combination of heavy alcohol consumption and HIV infection results in serious health problems and an increased risk of death. Although the mechanism is not clear, inflammation appears to play an important role. Zinc supplementation has anti-inflammatory properties. This study is designed to see if giving zinc supplementation to HIV-positive people who are heavy drinkers reduces the risk of serious health problems and death.

## 2. OVERVIEW OF STUDY DESIGN

### 2.1 STUDY AIMS AND OUTCOMES

138

139 ZINC aims to test the efficacy of zinc supplementation, compared to placebo, to:

140 1. Improve markers of mortality as measured by the change in VACS index between baseline and 18  
141 months—Primary outcome

142 2. Slow HIV disease progression as measured by change in CD4 cell count between baseline and 18  
143 months—Secondary outcome

144 3. Improve markers of AMI risk as measured by the Reynolds risk score at 18 months—Secondary  
145 outcome

146 4. Lower biomarker levels of microbial translocation and inflammation at 18 months—Secondary  
147 outcome

148

149 **2.2 STUDY HYPOTHESES**

150

151 We hypothesize that as compared with placebo, participants receiving zinc supplementation will have  
152 significantly:

153 Hypothesis 1- Smaller change in VACS (Primary);

154 Hypothesis 2- Greater change in CD4 cell counts (Secondary);

155 Hypothesis 3- Lower Reynolds risk score (Secondary);

156 Hypothesis 4- Lower biomarker levels of microbial translocation and inflammation (Secondary).

157

158 **2.3 STUDY DESIGN**

159

160 ZINC is a double-blinded randomized placebo-controlled trial of zinc supplementation (Zinc for  
161 INflammation and Chronic disease in HIV [ZINC]) among HIV-positive heavy drinkers in Russia to  
162 evaluate the efficacy of zinc to 1) improve markers of mortality, as measured by the VACS index; 2) slow  
163 HIV disease progression, as measured by CD4 cell count; 3) improve markers of coronary heart disease  
164 (CHD) risk, as measured by the Reynolds risk score and; 4) decrease microbial translocation and  
165 inflammation, as measured by serum biomarkers. Participants will receive study medication over 18  
166 months, with study visits occurring at 6, 12, and 18 months post enrollment, and shorter medication  
167 adherence visits at 6 weeks, 12 weeks, 9 months, and 15 months. ZINC RCT is nested within the Russia  
168 ARCH cohort of the Uganda, Russia, Boston Alcohol Network for Alcohol Research Collaboration on  
169 HIV/AIDS (URBAN ARCH) Consortium, which aims to understand how alcohol use impacts people  
170 affected by HIV and develop interventions to reduce alcohol use and alcohol and HIV-related

consequences in this population.

[figure not shown]

## 2.4 STUDY SITE

Recruitment, enrollment, and all study visits will take place at the Laboratory of Clinical Pharmacology of Addictions at the First St. Petersburg Pavlov State Medical University (PSMU) in St. Petersburg, Russia. PSMU is the major educational, scientific, and clinical medical institution for northwestern Russia. Blood specimens will be processed and analyzed at ImmunoBioService (IBS) and Pasteur Laboratories.

## 2.5 INCLUSION CRITERIA

To be eligible to participate in the trial, participants must meet the following inclusion criteria:

1. 18-70 years old
2. Documented HIV-positive
3. Documented ART-naïve status
4. Heavy alcohol consumption (i.e., NIAAA risky drinking criteria: > 4 standard drinks in a day [or > 14 standard drinks/week] for men and > 3/day [or 7/week] for women) in the past 30 days
5. Ability to provide contact information for two contacts to assist with follow-up
6. Stable address within St. Petersburg or districts within 100 kilometers of St. Petersburg
7. Possession of a home or mobile phone.

## 2.6 EXCLUSION CRITERIA AT STUDY ENTRY

1. Not fluent in Russian
2. Cognitive impairment resulting in inability to provide informed consent based on research assessor (RA) assessment
3. Pregnancy, planning to become pregnant, or breast feeding

## 2.7 RECRUITMENT GOALS

The study aims to recruit 250 participants.

Note: With permission from NIAAA, the study exceeded its target enrollment of 250 to enroll 254 heavy drinkers to account for enrollment of 4 participants who were subsequently discovered to be HIV-negative.

### 2.7.A. SAMPLE SIZE CALCULATION AND POWER

Power was calculated for the overall primary study endpoint (change in VACS index score). Power calculations assumed a two-sided hypothesis test, with a significance level of 0.05. It was expected that 250 participants would be enrolled into the study. We anticipated 20% loss to follow-up due to death and participant withdrawal. Based on the VACS study, the standard deviation of the change in VACS index score from initiation of ART to after one year was 25. We expect the standard deviation will be similar in this study. Given these assumptions and with 200 evaluable participants (assuming 20% loss to follow-up, and 100 participants in each arm), the study is anticipated to have 80% power to detect a difference between the placebo and zinc groups in their mean changes in VACS index score over the 18-month period as small as 10 (e.g. 20 vs. 10 for the placebo and zinc groups, respectively) using a two-sided t-test.

Aim 2: To test the efficacy of zinc supplementation compared to placebo to slow HIV disease progression as measured by CD4 cell count. We anticipate analyzing log transformed values of change in CD4 cell count due to possible skewness in the data. Group differences will be back transformed from the natural log scale and therefore the parameter of interest is the ratio of the mean changes in CD4 cell count from baseline to 18 months for the zinc group relative to the placebo group, where change is defined as CD4 count at baseline - CD4 count at 18 months. The estimated coefficient of variation for the change in CD4 cell count from baseline to 18 months (baseline - 18 months) is 0.20 cells/ $\mu$ L. Given these assumptions, with 200 evaluable participants (100 in the zinc and placebo arms), the study will have 96.3% power to detect a ratio of 0.90 (zinc:placebo) between the mean changes of CD4 counts for the zinc and placebo groups using a two-sided t-test.

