## 8.2 ADDITIONAL EXPLORATORY ANALYSES

**Effect of zinc over time:** The main analyses will focus on the VACS index, our primary outcome, and other secondary outcomes at the 18 month time point as the primary interest is in evaluating the long-term effects of zinc and it is anticipated that effects will change over time. Additional analyses using generalized linear mixed effects models will be used to incorporate the repeated measures for each outcome in the same model and will test for possible zinc by time interactions (e.g. does the effect of zinc increase over time). The mixed effects models will include subject-specific random intercepts and slopes to account for the correlation due to having repeated observations for each subject. The mixed models will be implemented in SAS PROC MIXED. In addition to the mixed effects model, we will also consider additional confirmatory models such as the general linear model for correlated data using an autoregressive covariance structure.

**Moderators and Mediators:** Additional analyses will also be conducted to evaluate whether the effects of zinc depend on level of alcohol consumption. Models will be fit including a zinc by heavy alcohol interaction term. If the interaction is significant, subsequent stratified analyses will be conducted to evaluate the effect of zinc in each alcohol group. Given the potentially complex role of ART use in the relationship between zinc and each outcome, various analyses will be considered to explore its possible role. First, it is not expected that initiation of ART use during follow-up to differ by randomized arm, however exploratory analyses will be conducted to compare initiation of ART use by randomized group. In addition, longitudinal analyses will be conducted including ART use as a time dependent variable in

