## SECTION 1: INTRODUCTION

### 1.1 STUDY HYPOTHESES

We hypothesize that as compared with placebo, participants receiving zinc supplementation will have significantly:

Hypothesis 1- Smaller change in VACS (Primary);

Hypothesis 2- Greater change in CD4 cell counts (Secondary);

Hypothesis 3- Lower Reynolds risk score (Secondary);

Hypothesis 4- Lower biomarker levels of microbial translocation and inflammation (Secondary).

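### The 96.3% power stated for CD4 rests on an unsourced coefficient of variation of 0.20 for a change score, on a log scale undefined for anyone whose CD4 does not fall

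*Supplement*

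**What the plan says.** Protocol 2.7.A sets out Aim 2 as follows.

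- Scale: "We anticipate analyzing log transformed values of change in CD4 cell count due to possible skewness in the data".
- Sign: the parameter is the back-transformed ratio of mean changes, zinc to placebo, "where change is defined as CD4 count at baseline - CD4 count at 18 months".
- Variability: "The estimated coefficient of variation for the change in CD4 cell count from baseline to 18 months (baseline - 18 months) is 0.20", followed by the unit cells/µL.
- Power, with 100 evaluable participants per arm: "the study will have 96.3% power to detect a ratio of 0.90 (zinc:placebo) between the mean changes of CD4 counts".

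SAP 2.3 refers back to this section without change. SAP 5.1 keeps CD4 change from baseline to 18 months as the Aim 2 outcome. Protocol 8.1 and SAP 5.2 do not fix the log scale. They call for linear regression if the data are normal, a transformation (log is the example given) if they are skewed, and median regression if no suitable transformation is found.

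Protocol 2.2 and SAP 1.1 give the direction as "Hypothesis 2- Greater change in CD4 cell counts (Secondary". Participants are ART-naïve at entry. Starting ART during follow-up is foreseen: Protocol 8.2 says "exploratory analyses will be conducted to compare initiation of ART use by randomized group", and SAP 5.4 adds chi-square and log-rank comparisons.

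**The concern.** With change defined as baseline minus 18 months, a participant whose CD4 is unchanged scores zero and one whose CD4 rises scores below zero. Neither has a logarithm. Starting ART would be expected to raise CD4, so such participants are foreseeable, yet no section says how they would be handled on the log scale. The ratio of mean changes has a related weakness: it becomes unstable when a mean change is near zero and loses its meaning below zero.

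The power figure inherits the problem. A CV of 0.20 for a change score describes a trial in which essentially everyone's CD4 falls, and by a similar amount. If that is wrong, the 96.3% is not a credible property of the design, and a null CD4 result could be read as better-powered evidence of no effect than it is.

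The sign is also inconsistent. In 2.7.A a benefit of zinc is a smaller change (ratio 0.90), while Hypothesis 2 predicts a greater one.

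**Working it through.** **Inputs (Protocol 2.7.A).** "Power calculations assumed a two-sided hypothesis test, with a significance level of 0.05"; 100 per arm; ratio 0.90; CV of the change 0.20; two-sample t-test on the natural-log scale.

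**1. Reproduce the plan's figure.**

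- Log-scale SD = √ln(1 + CV²) = √ln(1.04) = 0.1980.
- Difference = |ln 0.90| = 0.1054.
- Standardised difference = 0.1054 / 0.1980 = 0.532.
- Noncentrality = 0.532 × √(100/2) = 3.76.
- Power from the noncentral t with 198 df = **96.28%**, which matches the stated 96.3%.

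Using 0.20 directly as the log-scale SD gives 95.97%. An untransformed comparison (difference 0.10, SD 0.20) gives 94.0%. The lognormal t-test is therefore the calculation behind the figure.

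**2. What a CV of 0.20 implies.** The mean fall lies 1/0.20 = 5 SDs above zero. On a normal model, P(no fall) = Φ(−5) = 2.9 × 10⁻⁷, about 3 in 10 million.

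**3. A yardstick from the same section.** The VACS assumptions are an SD of change of 25 and example mean changes of 20 (placebo) and 10 (zinc). They imply change-score CVs of 25/20 = 1.25 and 25/10 = 2.5, about 6 to 12 times the value used for CD4. VACS is a different measure, so this does not give the CV for CD4. It does show how far 0.20 lies from the section's other change score.

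**4. Power as the CV varies.** The documents give no SD or mean for CD4 change, so every CV other than 0.20 is an assumption. Ratio 0.90, 100 per arm, two-sided 5% t-test:

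| CV of change | Power, log formula | Power, untransformed change | Placebo share with no fall (normal model), Φ(−1/CV) |
|---|---|---|---|
| 0.20 | 96% | 94% | 3 in 10 million |
| 0.25 | 85% | 80% | below 0.01% |
| 0.30 | 71% | 65% | 0.04% |
| 0.50 | 35% | 29% | 2% |
| 1.0 | 14% | 11% | 16% |
| 1.25 | 12% | 9% | 21% |
| 1.5 | 10% | 8% | 25% |
| 2.5 | 8% | 6% | 34% |

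Log-formula power crosses 80% at a CV of about 0.27. The log formula assumes a lognormal change, which is never zero or negative. The last column assumes a normal change, so it belongs with the untransformed column.

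**5. If 0.20 were really the CV of each count.** This is one possible explanation; nothing in the documents confirms it. Assume mean counts of 300 to 500, a mean fall of 100 and within-person correlation r. Then the SD of change = 0.20 × mean count × √(2(1 − r)). Power is for a 10-cell difference (a 10% smaller fall), untransformed.

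| r (assumed) | SD of change | Power | Share with no fall |
|---|---|---|---|
| 0 | 85–141 | 8–13% | 12–24% |
| 0.7 | 46–77 | 15–33% | 2–10% |
| 0.9 | 27–45 | 35–75% | at most about 1% |

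The result depends heavily on r, but no row reaches 96.3%.

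**6. Sign.** Under 2.7.A, a ratio of 0.90 means a smaller fall on zinc, which is the benefit. Under Hypothesis 2 the benefit is a greater change. Both can hold only if Hypothesis 2 uses 18 months minus baseline, which no section says.

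**The case against.** Several points on the other side stand.

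- A reader might infer that 96.3% is a miscalculation. It is not: it follows exactly from the stated inputs. The fault is in the assumed CV and the scale.
- A reader might infer that the CD4 analysis will drop everyone whose CD4 did not fall, and so select on the outcome. The documents do not say so. Section 2.7.A only anticipates the log. SAP 5.2 makes it conditional on skewness and offers median regression. SAP 3.3 puts all randomised participants in the ITT population, and SAP 5.3 makes multiple imputation the primary ITT analysis. A statistician could reasonably call an undefined log an inappropriate transformation and move to medians.
- A reader might infer that the true CD4 power is known to be very low. It is not. Without an SD of change only a range is available, and assuming independent counts is unfavourable, as step 5 shows.
- The sign conflict does not affect inference. Tests are two-sided, SAP 5.2 states the direction plainly as higher CD4 counts, and the baseline-minus-18-months definition appears only in the power section.
- CD4 is secondary. The trial was sized on VACS change, and that 80% reproduces (80.4% by t-test).

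What the objection does not remove: the SAP's trigger for transforming is skewness, not the presence of non-positive values, and log is its only named example. Untransformed change and median regression both abandon the ratio of mean changes, so the stated power describes neither fallback.

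**Conclusion.** Wrong as written, of moderate severity, for a secondary endpoint. The 96.3% is correctly computed from an input that has no source, carries an impossible unit, and implies that virtually no participant's CD4 holds steady or rises. It should not stand as an assurance for Aim 2. The margin is thin: power is under 80% beyond a CV of about 0.27, and about 35% to 10% for assumed CVs of 0.5 to 1.5. The anticipated scale cannot be computed for foreseeable participants. A valid analysis remains open under SAP 5.2, and neither the sample size nor the primary analysis depends on this figure. That a log is undefined at or below zero needs no assumption; every alternative power figure rests on an assumed CV or correlation.

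**What to change.** - **Protocol 2.7.A:** remove the log of change and the ratio of mean changes. Withdraw the 96.3%, or restate it as the detectable difference in cells/µL with 100 per arm for a stated, sourced SD. As a guide, the VACS calculation shows that 100 per arm gives about 80% power for 10/25 = 0.40 SD.
- **SAP 5.2:** state that the log is not applied to CD4 change. Analyse 18-month CD4 (or untransformed change) adjusted for baseline CD4 and the two stratification factors. If a transformation is needed, apply it to the count, not to the difference. At present baseline CD4 enters only as a potential confounder if the arms differ on it.
- **Protocol 2.2 and 2.7.A, SAP 1.1 and 5.1:** define change as 18 months minus baseline throughout, so that greater means benefit.

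The cost is wording in both documents and a less favourable stated power for Aim 2. Recruitment, visits and the primary analysis are unaffected.

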### 2.3 SAMPLE SIZE

See section 2.7.A. of Study Protocol

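### The 96.3% power stated for CD4 (Aim 2) rests on an unsourced CV of 0.20 for a change score, which leaves no room for CD4 gains although the plan foresees ART starts

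*Supplement*

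**What the plan says.** Protocol section 2.7.A sizes the trial on the change in VACS index and then adds a power statement for Aim 2. Change in CD4 is defined as the baseline count minus the 18-month count, so a fall is positive and a gain is negative. The authors expect to analyse the natural log of this change and to report the zinc-to-placebo ratio of mean changes.

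- Variability: "The estimated coefficient of variation for the change in CD4 cell count from baseline to 18 months (baseline - 18 months) is 0.20". The figure is printed with the unit cells/µL, and no source is cited.
- Size: "with 200 evaluable participants (100 in the zinc and placebo arms".
- Test: "Power calculations assumed a two-sided hypothesis test, with a significance level of 0.05".
- Result: "the study will have 96.3% power to detect a ratio of 0.90 (zinc:placebo) between the mean changes of CD4 counts".

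The SAP adds nothing to this. Its section 2.3 reads "See section 2.7.A. of Study Protocol".

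On ART, participants must be treatment-naïve only at enrolment. Protocol section 8.2 says that "exploratory analyses will be conducted to compare initiation of ART use by randomized group" and also treats ART use as a time-dependent covariate, possible effect modifier and possible mediator. SAP section 5.4 adds chi-square and log-rank comparisons of ART initiation by 18 months. The power paragraph makes no allowance for ART starts.

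**The concern.** A CV of 0.20 may be reasonable for a quantity that is always positive and well away from zero. A within-person difference between two counts is not such a quantity, because it can take either sign. A CV of 0.20 says that the spread of individual changes is only one fifth of the average fall. For example, an average fall of 100 cells/µL would come with an SD of 20. Almost everyone would have to fall, by a similar amount. A CV also has no unit, so the printed cells/µL needs correcting in any case.

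The assumption that everyone falls is also what makes the planned parameter computable, since the log of the change does not exist for anyone whose CD4 is stable or rises. The plan nevertheless expects some participants to start ART, and it is hard to see how none of them would gain CD4.

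What is at stake is how Aim 2 is described. The protocol presents it as almost certain to detect a 10% effect, and a null CD4 result could be read against that claim.

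**Working it through.** **Inputs (all from 2.7.A).** Two-sided alpha 0.05; 250 enrolled less 20% loss gives 250 × 0.80 = 200 evaluable, 100 per arm; ratio 0.90; CV 0.20.

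**1. Reproduce the plan's figure.** For a ratio of means under a lognormal model:
- SD(log) = √ln(1 + 0.20²) = 0.198
- SE = 0.198 × √(2/100) = 0.0280
- |ln 0.90| / SE = 0.1054 / 0.0280 = 3.76
- noncentral t with 198 df: power 96.28%

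This matches the printed 96.3%, so the CV of 0.20 was indeed applied to the change itself.

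**2. What the input implies.** Zero lies 1/0.20 = 5 SDs below the mean fall. Under a normal model the proportion with no fall is Φ(−5) = 2.9 × 10⁻⁷, fewer than one in a million. Under the lognormal model it is exactly zero.

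**3. Sensitivity to the CV.** The documents give no other value, so the CVs below are assumptions. Because the question is what happens when some changes are negative, I use a raw-scale t-test, which allows them. The difference is 10% of the placebo mean, the common SD is CV × placebo mean, and the noncentrality is 0.10 / (CV × √(2/100)).

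| CV | Noncentrality | Power | Share gaining CD4 (normal model) |
|---|---|---|---|
| 0.20 | 3.54 | 94.0% | 2.9 × 10⁻⁷ |
| 0.25 | 2.83 | 80.4% | 3.2 × 10⁻⁵ |
| 0.30 | 2.36 | 65.0% | 0.04% |
| 0.50 | 1.41 | 29.1% | 2.3% |
| 1.0 | 0.71 | 10.8% | 15.9% |

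The lognormal formula gives 71%, 35% and 14% at CV 0.30, 0.50 and 1.0. The pattern is the same, but that model cannot produce a CD4 gain at any CV, so it is not the one to rely on here.

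**4. The same question from the other side.** If a proportion p gains CD4 under a normal model, the CV is 1 / z(1−p):
- p = 1%: CV = 1/2.326 = 0.43, power about 37%
- p = 5%: CV = 1/1.645 = 0.61, power about 21%

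**5. Check on the primary outcome.** With SD 25, difference 10 and 100 per arm, the t-test gives 80.4%, in line with the stated 80%.

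**The case against.** The strongest reply is that little depends on this figure. CD4 is a secondary outcome, the Aim 2 paragraph sets no sample size, and no test or decision rule in the SAP uses the 96.3%. SAP section 3.1 requires confidence intervals, which will show the precision actually achieved. All of this stands. It limits the consequence of the point but does not support the number.

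A second reply is that CD4 can still be analysed if some changes are negative. That also stands. Protocol 8.1 and SAP 5.2 prescribe linear regression for normal data, a transformation if the data are skewed, and median regression if no transformation works. The logged change is only what 2.7.A anticipates, so a reader who concludes that Aim 2 has no valid analysis goes too far.

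A third reply is that the true variability is unknown, which is correct. A reader might infer that the real power is some specific low figure, such as 11%. The documents cannot show that, because they give no mean or SD of the CD4 change and no ART start rate. Nor can a CV be borrowed from the VACS planning figures, where the effect is "as small as 10 (e.g. 20 vs. 10 for the placebo and zinc groups, respectively" with an SD of 25 (25/20 = 1.25). That SD comes from another cohort's first year on ART, the 20 is one half of an example, and the variable is a different one.

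**Conclusion.** The point holds as a fault in an input, not in the arithmetic. The 96.3% follows correctly from a CV of 0.20, but that CV is unsourced and implies that essentially no participant's CD4 rises, which conflicts with the plan's own provision for ART starts. The stated power is therefore unsupported.

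The direction is firm. Under a normal model, 80% power for a 10% difference already requires a CV of about 0.25, at which only about 3 in 100,000 participants would gain CD4. The size is not known: about 94% down to 11% for CVs from 0.20 to 1.0 is a sensitivity range, not an estimate.

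This rests on raw-scale normal changes, equal SDs, 100 evaluable per arm, and the general expectation that at least some participants who start ART gain CD4. The documents do not quantify that last item.

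A reader might also infer that the trial as a whole is too small. The documents do not support this: the sample size was set on the VACS index, and that calculation reproduces.

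**What to change.** In protocol 2.7.A, withdraw the 96.3% and the ratio of logged changes. Restate Aim 2 in one of two ways:

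- **Difference in mean CD4 change, in cells/µL.** Give an SD of the change with its source, or a range of SDs, chosen to allow for ART starts. With 100 per arm, the difference detectable with 80% power is (1.960 + 0.842) × √(2/100) × SD, or about 0.40 × SD, so each SD in the range converts directly.
- **Ratio of 18-month CD4 counts on the log scale, adjusted for baseline.** Counts are positive, so the log does not depend on everyone falling.

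Do not fill the gap with a CV taken from the VACS example, and do not print a range of powers from the lognormal model of the change, since that model excludes CD4 gains. State the sign convention at the same time: Hypothesis 2 expects a greater change with zinc, whereas 2.7.A, counting falls as positive, powers for a smaller one. SAP 2.3 needs no edit, because it refers to 2.7.A.

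The cost is wording only. No participants are added and the primary analysis is untouched. The only downside is a less favourable stated figure for a secondary aim.
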